## Abstract

**Background:**

Attention-deficit hyperactivity disorder (ADHD) is a mental disorder beginning in childhood, and about half of patients have symptoms lasting into adulthood. Adult ADHD causes various impairments of emotional, self-esteem, and executive function and life quality aspects. Furthermore, adverse outcomes include academic and occupational failures, traffic accidents and substance abuse, which would be a family and social burden. A combination of medication and psychotherapy is recommended as the treatment for adult ADHD, and cognitive behavioral therapy (CBT) has been validated mostly with evidence-based researches. However, there has been a lack of randomized controlled trials of CBT for patients in China. Moreover, booster sessions of CBT for other disorders have proven effective in reducing recurrence and improving long-term outcomes, which has not been investigated for adult ADHD. This study will testify to the effect of CBT and explore the efficacy of subsequent booster sessions on adult ADHD.

**Methods/Design:**

It is a three-armed randomized controlled trial to evaluate the efficacy of 12 weeks of CBT based on the published and validated manual and its booster sessions. The 12 weeks of CBT will be conducted weekly and will end at the 12th week, and then the booster sessions will be conducted monthly and end at the 24th week. There are three randomized groups, including a CBT with booster sessions group, a CBT group and a waiting group. Participants are outpatients of the Peking University Sixth Hospital who are diagnosed as having adult ADHD. The Primary efficacy endpoints are the scores of ADHD core symptoms at 12 and 24 weeks. Secondary endpoints include emotion, executive function, self-esteem, life quality and functional magnetic resonance imaging (fMRI) data at different time points, and the change within every group will also be analyzed.

**Discussion:**

This is the first study to explore the efficacy of booster sessions of CBT in adult ADHD as far as we know. The results might increase proof of efficacy of CBT for adult ADHD in China, and the results showing efficacy of the booster sessions would also benefit our clinical practice.

**Trial registration:**

Current Controlled Trials: NCT02062411, date of registration: 12 February 2014.

## Background

Attention-deficit hyperactivity disorder (ADHD) begins in childhood [1], and 50% of patients have symptoms lasting into adulthood [2]. The prevalence of adult ADHD is about 5% [3]. There are different adverse outcomes along with adult ADHD including comorbidities as depression and anxiety; cognitive function impairment; social dysfunctions such as procrastination, dropping out of school, and being laid off; increasing rates of traffic accidents; substance abuse; and decreases in quality of life [4-8]. This disease could cause a great burden of society, and the human capital value was reported as $4,336 per worker for a single year in the United States [9]. The clinical treatment guideline recommends a combination of medication and psychotherapy as the first line therapy method for adult ADHD [10,11], and the cognitive behavioral therapy (CBT) has been validated mostly with evidence-based researches [12-15].

The efficacy of CBT in adult ADHD has been proven in several randomized studies on the aspects of core symptoms, emotion, self-esteem and time-management strategies [12-15]. Studies also found the efficacy of CBT was superior to relaxation with educational support [13] and computerized cognitive training [16]. Compared with medication, CBT could also improve patients’ ADHD symptoms without previous medical treatment, which might suggest that the mechanism of CBT did not fully rely on medication [14]. However, the previous studies mainly focused on some selected aspects of CBT’s efficacy, and the multidimensional impairments that proved to be prominent for adult ADHD patients [4-8] had not been tested in the same group of subjects, which left the measurement of CBT’s efficacy remaining to be explored [17]. Our group’s self-control study also found preliminary evidence of the efficacy of 12 weeks of CBT in a Chinese population [18,19], which needs to be further validated in a randomized controlled study.

A review of CBT studies for adult ADHD emphasizes that evidence of long-term outcomes is limited [17]. Through the follow-up of treated patients from our group study, which only used 12 weeks of CBT as described in the manual [18], we found that patients forgot the skills they learned in CBT and had difficulties in applying them into practice in real life. The booster sessions were previously used in behavior therapy to achieve sustaining results, and a review of 30 clinical trials concluded that the booster sessions were useful in maintaining behavioral change [20]. With regard to CBT, according to studies covering depression [21,22], bipolar disorder [23], panic disorder [24] and binge eating disorder [25], providing the booster sessions or the maintaining treatment after the completion of CBT would reduce the recurrence rate and benefit the long-term effect. Furthermore, the latest meta-analyses found that CBT with booster sessions was more effective and had more sustainable outcomes for children with mood or anxiety disorders [26]. To date, three CBT studies for adult ADHD have included periods as booster sessions [13,14,27]; however, the specific effects of this process have not been investigated. In Safren’s study, there is an optional session that contains review and summary of the previous lessons [13]. There were two booster sessions in Weiss’s research at 15 and 20 weeks [14], and 10 booster sessions monthly in Philipsen’s study protocol after 12 weeks of group therapy [27]. None of these above studies considered these periods as separate from the treatment or explored their role in the integrated treatment.

The integration of known CBT interventions for other disorders in adult ADHD remain to be explored [17]. So, we wonder whether the booster sessions could help CBT in fulfilling the skill-teaching and practicing missions, thereby prolonging the efficacy for adults with ADHD. This study is conducted to test whether CBT is effective in the treatment of attention-deficit and emotional, executive and social impairments due to ADHD in a randomized controlled design and to explore the role booster sessions played in the CBT process.

### Objectives/hypotheses

The primary research questions are as follow: (1) Is CBT effective in the treatment of adult ADHD and related problems? and (2) Is the treatment effect of CBT with booster sessions superior to that of CBT only?

There are still other questions: (1) Would booster sessions improve the patients’ satisfaction at evaluation? The subjective evaluation would reflect the acceptability of the treatment, especially in psychotherapy, and these measurements might reflect factors that work other than outcomes of scales or behavioral tests [15,28]. (2) Are there some significant factors that can predict or influence the outcome, including symptom severity, comorbidity, social and economic status, and neuropsychological or neuroimaging biological markers? The role of baseline situations in CBT for adult ADHD remains unclear, and the possible biological markers might benefit finding the “working factors” in CBT [17,29,30]. (3) Would the effects of CBT cause some neuroimaging changes? The neuroimaging methods would provide the biological evidence of treatment and benefit exploring the mechanism of psychotherapy [29]. (4) Finally, considering the limited evidence of long-term effects [17,30], how long the outcomes last would also be evaluated.

The hypothesis of this study is that CBT reduces ADHD symptoms compared to nonintervention, and CBT with booster sessions reduces more ADHD symptoms compared to CBT only.

## Methods/Design

### Study design

We use a three-armed study design in order to evaluate the effect of CBT on ADHD adults compared with no intervention condition and the effect of 12 weeks CBT with booster sessions versus 12 weeks CBT only. There are three randomized groups, including a CBT with booster sessions group (group 1), a CBT group (group 2) and a waiting group (group 3).

The primary and secondary outcomes will be evaluated at baseline (T1), after 12 weeks of treatment (T2) and after three booster sessions, which is at 24 weeks (T3). Moreover, two ADHD symptom evaluation scales and two emotion evaluation scales will be rated weekly during the 12 weeks of treatment in order to monitor the changes. Patients of the CBT with booster sessions group (group 1) will be followed up at 36 weeks and 48 weeks. Furthermore, the follow-up will be conducted at 24 weeks, 36 weeks and 48 weeks for patients of the CBT group (group 2), and will be at 12 weeks for the waiting group (group 3) patients (Figure 1). Considering the interest of the waiting group patients, on request, we will provide them with 12 weeks of CBT at no charge after the study.

**Figure 1 Fig1:**
[figure not shown]
Trial flow. W, week; CBT, cognitive behavioral therapy.

This study is conducted in the Peking University Sixth Hospital and funded by Beijing Municipal Science and Technology Commission. The research is based on good clinical practice standards (GCP) and the CONSORT statement [31,32], which received ethics approval from Ethics Committee of the Sixth Hospital of Peking University ((2013) Ethics review number (42)). It has been registered in ClinicalTrials.gov (NCT02062411).

### Intervention

In this study, 12 weeks of CBT is being conducted according to a published and validated [12,13] manual (Mastering Your Adult ADHD: A Cognitive-Behavioral Therapy Approach, Safren SA, Perlman CA, Sprich S, Otto MW, 2005) [33]. The original manual consisted of three core modules and two optional modules, and we put all five modules into practice. The first part (five sessions) consists of psychoeducation; supportive relationships; and organizational skills such as using a calendar system, breaking tasks into small steps and evaluating the benefits and shortcomings of choices. The second part (two sessions) is mainly about coping with distractibility, including the skill to record distractive thoughts and management of the surroundings. The third part (three sessions) is cognitive restructuring, which helps patients identify the maladjusted automatic thoughts and change them into adaptive ones. The last part (two sessions) includes dealing with procrastination with all the learned skills and summary. All the 12 sessions are conducted once a week at weekends. The English manual was translated into Chinese by our group’s senior psychiatrists who received psychotherapy training, and the Chinese edition was applied to two different groups of patients in self-control studies, which was effective for reducing ADHD symptoms and improving everyday life executive function, self-esteem and life quality [18,19].

The booster sessions are designed according to the definition of booster sessions in studies of ADHD [13,14,27] and other diseases [21-25], the main goal of which is consolidating the skills learned and developing strategies dealing with recurrence or relapse. Thus, the booster sessions in the present study contain the induction of the first three parts above and practicing activities based on the patients’ questions in the real world. The first booster session includes a summary of the first organizational part of the 12-week manual. It also includes other important time-management skills such as goal setting, reward system and authorizing others [34], and a discussion of the practice questions through role-play. The second booster session consists of the summary of the distractibility part, the discussion of the relationship between distractibility and procrastination, and making a self-coping list. The last booster session includes a summary of the cognition part, the discussion of automatic thoughts of real situation by role-play, and the relationship between automatic thoughts and procrastination. These three booster sessions are conducted monthly after the complement of 12 weeks of CBT.

### Participants

The subjects mainly are outpatients of the Peking University Sixth Hospital. Patients who read the recruitment on the internet, come to the outpatient service and meet the inclusion criteria will also be included. All subjects will be fully informed about the research before being asked to sign the informed consent form.

Patients with adult ADHD are recruited. With regard to the former treatment, we include people who have been stable on medications for adult ADHD for at least 2 months (drug dose was adjusted within 10% in last two months [13]). The key inclusion criteria include the following:Outpatients from Peking University Sixth Hospital, who have received a diagnosis of adult ADHD through Conners’ Adult ADHD Diagnostic Interview [35] based on Diagnostic and statistical manual of mental disorders, Fourth Edition (DSM-IV).Patients who are either medication naive or have been stable on medications (for the treatment of ADHD, drug dosage adjustment in last two months was below 10% [12]) for adult ADHD for at least 2 months.

Furthermore, patients with comorbidity that may influence the study outcomes or need extra treatment are excluded. Patients who are at risk for suicide, in unstable physical condition, or have received psychological treatment will be excluded. To make some cognition function assessments possible, people who are older than 45 years old or have intelligence quotient (IQ) less than 90 will be excluded. The key exclusion criteria include the following:Severe major depression, clinically significant panic disorder, bipolar disorder, organic mental disorders, psychotic disorders, or pervasive developmental disordersAge older than 45, which might influence outcomes of cognitive tests [36] or IQ less than 90 [12]Suicide riskUnstable physical condition, which needs medical treatment prior to ADHD such as active hepatitis and angina pectorisPrior or present participation in other psychological therapies.

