### Blinding and quality control

There is an independent statistician who conducts the randomization of patients and analyzes the research results. The participants and endpoint assessors are kept blind during the study. Only the principal investigator is informed of the randomization results at first, and the psychotherapists are told when the 12 weeks of CBT is completed.

There are two psychiatrists who conduct the CBT and they have received same systematic psychotherapy training, including CBT training. They received psychological training courses held by the Peking University Sixth Hospital and the Chinese Psychological Society. One psychiatrist is in charge of the therapy, and the other is the recorder who writes down all the sessions. There also are two supervisors, including a psychiatrist and a psychotherapist. Regular discussion and supervision are conducted during the study. The assessors are mainly postgraduate students of psychiatry, and they are trained to use all the measurement tools and the consistency is rated.

The principal investigator monitors the research progress and ensures all the steps are taken according the original protocol, and the Ethics Committee supervises the interests of subjects such as safety and confidentiality.

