### Power

It is a noninferiority randomized controlled study, and the primary outcome measure is the mean difference of the ADHD-RS scores between groups. Since there was no relevant study that included booster sessions for adult ADHD, we used the results of a self-controlled preliminary experimental study. At baseline, the score of the ADHD rating scale was 29.80 ± 7.67 (n = 15), after CBT the score was 17.22 ± 7.62 (n = 18), and after booster sessions the score was 10.56 ± 4.98 (n = 16). We assume the drop-out rate is 10%, because the previous studies showed good compliance, and the outpatients are willing to participate [18,19]. So with the power of 80% and alpha of 5% and based on the formula (n = 2[(tα + tβ)*σ/δ]^2, n means number of subjects, tα means t value of alpha, tβ means t value of beta, σ means population standard deviation, δ means deviation), the sample size is about 73 subjects including 15 patients in the waiting group (group 3), 29 in the CBT group (group 2), and 29 in the CBT with booster sessions group (group 1). The numbers of subjects varied in the three groups since the deviations (δ) of ADHD-RS scores after 12 week CBT and after booster sessions were different. Considering the real situation with recruitment, we separated it into three batches, with a total of 21, 24 and 28 subjects for one time (Table 2).

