### Statistical analysis

The main analysis is a two-group ANCOVA of ADHD symptoms, emotional symptomatology, executive function, impulsiveness, self-esteem and life quality at all time points with baseline scores as covariates. To estimate the changes with time in every group, the repeated measures ANOVA will also be used. Furthermore, the neuroimaging data will be analyzed based on a voxel-by-voxel method and the general linear model with a one group by two time points design after pre-processing procedures. The statistics is based on intent-to-treat (ITT) analysis, and the last observation carried forward (LOCF) will be used to address the missing data.

The primary endpoints analysis is ANCOVA with ADHD-RS scores at 12 and 24 weeks separately as dependent variables and baseline ADHD-RS scores as covariates. Other variables that have correlation with ADHD-RS scores and clinical meanings will also be considered for covariates such as gender, age, IQ and education.

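### Baseline medication status, which splits the enrolled population in two, is not committed to as a covariate in the primary ANCOVAs and would enter only if it is found to correlate with ADHD-RS

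*Protocol article*

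**What the plan says.** Among the key inclusion criteria (Protocol article, Participants) is "Patients who are either medication naive or have been stable on medications" for adult ADHD. Stability means at least two months with dose adjustment below 10%. The sample is therefore a deliberate mix of untreated and treated patients, and each patient's category has to be settled before enrolment. The expected mix is not given.

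The Statistical analysis section states: "The primary endpoints analysis is ANCOVA with ADHD-RS scores at 12 and 24 weeks separately as dependent variables and baseline ADHD-RS scores as covariates". The Outcome measures section assigns the contrasts: group 2 v group 3 at 12 weeks, and group 1 v group 2 at 24 weeks. On further adjustment the plan adds: "Other variables that have correlation with ADHD-RS scores and clinical meanings will also be considered for covariates", with the examples "such as gender, age, IQ and education". Medication is not among them. Nor is it among the possible outcome predictors listed under Objectives/hypotheses, which are symptom severity, comorbidity, social and economic status, and biological markers.

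**The concern.** Baseline ADHD-RS does not mean the same thing in the two groups. In a medicated patient it is what remains on drug; in a naive patient it is the untreated level. Two patients with equal baseline scores need not follow the same course over 12 or 24 weeks, so medication status may carry prognostic information beyond the baseline score.

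Two things are at stake. The first is precision: any outcome variance that medication status explains stays in the error term if it is left out, and any chance difference in medicated share between small arms goes into the estimated treatment effect. The second is pre-specification: whether this variable enters the primary model depends on a correlation seen in the data. The section does not say how strong that correlation must be, or whether it is with the baseline or the follow-up score.

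**Working it through.** **The plan's own figures.** The article gives no number for medicated share or medication effect, so there is nothing to reproduce on this exact point. The Power section supplies only the scale. (Its formula, at two-sided 5% and 80% power, gives 6-7 per arm for 12.58 points. For 6.66 points it gives 16-17 with the pooled SD, or 21-22 with SD 7.62. All are before dropout, against the stated 15 and 29. That mismatch is a separate matter, and nothing below depends on it.)

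**Inputs from the Power section and Table 2**
- Arms: 29 (group 1), 29 (group 2), 15 (group 3). Dropout is 10%, so 29 × 0.9 ≈ 26 completers per CBT arm.
- Pilot ADHD-RS: 29.80 (SD 7.67, n = 15), then 17.22 (SD 7.62, n = 18), then 10.56 (SD 4.98, n = 16).
- Differences: 29.80 − 17.22 = 12.58 and 17.22 − 10.56 = 6.66.
- Outcome SD: pooled √[(17 × 7.62² + 15 × 4.98²)/32] = 6.52. The largest pilot SD, 7.67, is the alternative.

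**Assumptions, not in the documents**
- Medicated share p = 0.2 to 0.5.
- Difference b between medicated and naive patients at follow-up, given baseline, = 2 to 6 points.
- Simple randomisation with respect to medication, since the article does not say otherwise.

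**Step 1: chance imbalance.** The SD of the difference in medicated share is √[p(1−p)(1/n₁ + 1/n₂)]. The probability of a gap of at least 20 percentage points is exact, from two independent binomials.

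| p | 29 v 29: SD | P(gap ≥ 20 points) | 29 v 15: SD | P(gap ≥ 20 points) |
|---|---|---|---|---|
| 0.2 | 0.105 | 7.0% | 0.127 | 11.2% |
| 0.3 | 0.120 | 11.4% | 0.146 | 16.6% |
| 0.5 | 0.131 | 14.8% | 0.159 | 20.4% |

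**Step 2: shift of the unadjusted estimate.** Shift = gap × b. For a 20-point gap it is 0.20 × 2 = 0.4 to 0.20 × 6 = 1.2 points. That is 3-10% of 12.58 (0.4/12.58 to 1.2/12.58) and 6-18% of 6.66 (0.4/6.66 to 1.2/6.66).

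**Step 3: variance explained.** R² = b²p(1−p)/SD².
- Smallest: b = 2, p = 0.2, SD 7.67: 4 × 0.16/58.8 = 1.1%.
- Middle: b = 4, p = 0.3, SD 6.52: 16 × 0.21/42.5 = 7.9%.
- Largest: b = 6, p = 0.5, SD 6.52: 36 × 0.25/42.5 = 21.2%.

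**Step 4: power at 24 weeks, 26 per arm.** Power = Φ[δ/(SD√(2/26)) − 1.96], with SD replaced by SD√(1−R²) after adjustment.

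| δ | SD | Without the term | With the term |
|---|---|---|---|
| 6.66 | 6.52 | 95.8% | 96.0-98.6% |
| 6.66 | 7.67 | 87.9% | 88.3-92.5% |
| 4.00 (60% of pilot) | 6.52 | 59.9% | 60.6-70.2% |
| 4.00 (60% of pilot) | 7.67 | 46.8% | 47.2-53.2% |

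**Step 5: would the correlation rule reliably pick the variable up?** Read as a squared correlation, the middle case is √0.079 = 0.28. The sampling error of a correlation is roughly 1/√(n−1): 0.15 for the 44 patients in the 12-week contrast and 0.13 for the 58 in the 24-week contrast. With 44 patients the observed value could lie anywhere from about 0 to 0.57 (0.28 ± 1.96 × 0.15). Selection could therefore go either way by chance.

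**The case against.** The strongest defence is that the covariate list is open. If medication status matters, it meets both stated conditions and can enter, so a reader who infers that the plan excludes it goes too far. That stands. But permission is not commitment, and Step 5 shows that entry by observed correlation is uncertain at these sample sizes.

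Second, baseline ADHD-RS already absorbs part of any medication effect, because stable patients are measured on their established treatment. The Background also cites evidence that CBT helped patients without previous medical treatment, which does not suggest that the two groups respond very differently. This also stands. It argues for the lower end of the assumed range, and b is defined as what remains after baseline.

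Third, a reader might infer that randomisation ignores medication status. The documents do not support that. The Blinding and quality control section says "There is an independent statistician who conducts the randomization of patients and analyzes the research results"; it names no stratification factor and rules none out, and a condensed article commonly leaves this to the full protocol. Stratifying from now on would in any case hardly help the 12-week contrast. Table 2 places all 15 waiting-group patients in batches 1 and 2 (45 of 73, 62%), and Trial status reports 66% randomised by June 2014. If batches filled in order, the waiting arm is complete.

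Fourth, one might call medication a known source of imbalance, or the imbalance likely. Neither is supported. No medication effect is documented, a gap of 20 points or more is absent in about 80% of trials or more, and chance imbalance under randomisation is not bias, since the standard error already allows for it.

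**Conclusion.** The point holds as a modest, inexpensive improvement. The plan mixes two medication groups by design, fixes only baseline ADHD-RS in the primary model, and leaves the variable that divides its population to be chosen by observed correlation.

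Its size depends on p = 0.2-0.5 and b = 2-6, neither of which the documents give. Over those ranges medication status explains about 1-21% of outcome variance, and a 20-point chance gap moves an unadjusted estimate by 0.4-1.2 ADHD-RS points. If the pilot differences are right, the gain in power is small. It becomes more useful if the booster effect is weaker than the uncontrolled pilot suggests, reaching about 10 percentage points at the most favourable corner of the assumptions (59.9% to 70.2%). Nothing here invalidates either primary comparison.

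**What to change.** In the Statistical analysis section, name baseline medication status (naive or stable on ADHD medication) as a fixed covariate beside baseline ADHD-RS in both primary ANCOVAs: 12 weeks, group 2 v group 3; and 24 weeks, group 1 v group 2. Do the same in the matching secondary ANCOVAs, beside each outcome's own baseline score. State that the term stays in whatever its observed correlation, and record the change before outcome data are examined by group.

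The cost is one degree of freedom. With intercept, group and baseline score in the model, residual degrees of freedom go from 44 − 3 = 41 to 40 at 12 weeks and from 58 − 3 = 55 to 54 at 24 weeks. No new data are needed, because eligibility screening already establishes the variable.
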